**Figure 1 F1:**
[figure not shown]
The data flow and the linkage of the Coordinate My Care dataset to the Whole System Integrated Care dataset. CAG, Confidentiality Advisory Group; CCR, Committee for Clinical Research; CMC, Coordinate My Care; DARS, Data Access Request Service; EOL, end-of-life; HRA, Health Research Authority; RM, Royal Marsden; SDE, secure data environment; WSIC, Whole Systems Integrated Care.

### Work package 1: exploration of EPaCCS records and association of social determinants of health in decision-making at the end of life (objectives 1A–1E)

In the first work package, a retrospective observational study, we hypothesise that this exploratory work package will help us understand the implementation of EPaCCS in terms of who creates EPaCCS and how EPaCCS are used, identify variation in their use and uptake, and clarify what information is included in these records.

The study will describe how EPaCCS are used, specifically who creates EPaCCS records and what information they encompass regarding individuals’ preferences for end-of-life care. The study will describe data fields across each of the three datasets and evaluate their completeness. Additionally, a descriptive analysis of the three EPaCCS datasets will be undertaken to describe the creation and content of the records across the three regions. These specific regions were chosen for being large metropolitan areas with varied levels of material deprivation and a high concentration of ethnic minority groups. This analysis will focus on the elements of ACP used to support decision-making at the end of life, which include documentation of the ceiling of treatment, resuscitation status, preferred place of care and preferred place of death. The study will also explore if changes are made to decision-making over time for each of these elements. As the three EPaCCS in the study contain data from different periods in time, we will take into account the different timescales during the analyses. The uptake of EPaCCS will be evaluated by describing the number of records created across different time periods and locations. The study will also investigate the setting of the initial record creation (hospital care, primary care, community care). Furthermore, the study will describe the clinical characteristics of patients such as their diagnosis, performance status, capacity for decision-making, living arrangements and expected prognosis. The study will also describe their socio-demographic characteristics with a particular emphasis on social determinants of health such as age, gender, socioeconomic position and ethnicity. The socioeconomic position will be defined using the Index of Multiple Deprivation (IMD), a standard scoring system based on a range of economic, social and housing data, creating a single deprivation score for each small area of the country. Using methodology previously employed in studies by the research team,^43 44^ an IMD score will be created for each patient based on their postcode which will reflect the deprivation data for the Lower-layer Super Output Area (LSOA) within which the postcode falls. Moreover, the study will investigate across sites the association between social determinants of health and the completion of each of the four previously mentioned ACP elements. Table 2 shows the mapping of the study objectives to data sources and eligibility criteria. Exclusion criteria for all data sources are participants who have chosen National Data Opt-Out and those who have withdrawn consent.

**Table 2 T2:** Mapping study objectives to data sources and eligibility to be included in analyses

Objectives		Data sources and eligibility
Work package 1		
1A	To describe and categorise the data fields and completeness of data contained within each EPaCCS register.	Anonymised EPaCCS data from London (CMC, n=140 000), Leeds (n=15 500) and Bradford (n=17 000)
1B	To describe the creation and content of EPaCCS records and elements relating to end-of-life decision-making preferences and ACP (ceiling of treatment, preferred place of care, and death and resuscitation status) in different regions across England.	
1C	To describe the socio-demographic and clinical characteristics of individuals who have created EPaCCS records in different regions across England.	
1D	To estimate associations between social determinants of health (socioeconomic position, ethnicity, age, and gender) and the completion of elements of ACP within EPaCCS.	
1E	To estimate associations between social determinants of health (socioeconomic position, ethnicity, age, and gender) and the creation of EPaCCS.	WSIC-CMC dataset of North West London deceased patients with/without EPaCCSLeeds decedent dataset 2021–2023 of deceased patients with/without EPaCCS
Work package 2		
2A	To explore the effect of EPaCCS on place of death and hospital use in the last 90 days of life.	WSIC-CMC dataset of North West London deceased patients with/without EPaCCSLeeds decedent dataset 2021–2023 of deceased patients with/without EPaCCS
2B	To explore the effect of an EPaCCS record on healthcare costs in the last 90 days of life.	WSIC-CMC dataset of North West London deceased patients with/without EPaCCS

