### Data sources

The study will use non-identifiable data from three EPaCCS across three distinct geographical locations in the UK, namely London, Leeds and Bradford, which combined have a population of 10.4 million people. These EPaCCS were introduced at different times within the same city and across different cities. This has led to natural variation in exposure, resulting in datasets that cover varying time periods: 2010–2022 in London, and 2015–2023 in Leeds and Bradford. Nonetheless, these EPaCCS are well established and contain a sufficient number of records, as illustrated in table 1, to enable meaningful individual site analyses and answer our research questions. Additional anonymised EPaCCS data from different regions will be considered if made available during the study. The sample size will be determined by the data available in the three datasets and will vary depending on the analysis.

**Table 1 T1:** EPaCCS and data availability

EPaCCS location	EPaCCS specific data
London EPaCCS	Coordinate My Care (CMC) served as the commissioned EPaCCS in London from 2010 to 2022, during which time it was also the largest UK EPaCCS. Covering 32 CCGs serving a population of 8.9 million, this EPaCCS dataset reflects a diverse urban patient population in terms of diagnosis, ethnicity and socioeconomic background. CMC records comprise data from various healthcare settings, including primary and secondary care, hospices and nursing homes. The dataset encompasses demographics, diagnoses, care preferences, the ceiling of treatment, resuscitation status, living circumstances, prognosis, performance status, date and place of death. Additionally, data is available regarding how often the record was accessed by urgent and non-urgent healthcare workers. In later years, patients had the option of starting a ‘MyCMC’ plan, whereby they use a patient portal to input some data themselves. The anticipated numbers for inclusion in the dataset are 140 000 records, of which 100 000 are for deceased patients.

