Leeds EPaCCS	The Leeds EPaCCS dataset represents a combined dataset from community palliative care providers that includes all primary care practices and two city hospice sites (St Gemma’s Hospice and Wheatfields Hospice) and limited secondary care data (eg, unplanned hospital admissions in the last 90 days of life). This dataset encompasses decedent patient records spanning from 2015 to 2023. It includes linked healthcare records data including primary and secondary care data, such as hospital admissions and diagnosis of severe mental illness or learning disability. The EPaCCS in Leeds covers the entirety of the former Leeds CCG serving a population of around 870 000 people through 94 general practitioners (GP) practices. Since 2019, approximately 50% of all people who die in Leeds have an EPaCCS.^67^ Data for all deaths across Leeds from 2021 to 2023 are also available, including decedents without EPaCCS. This will enable comparative analysis between patients with or without EPaCCS records. The anticipated number of records for inclusion is 15 500 decedent records.
Bradford EPaCCS	The Bradford EPaCCS dataset is collected and shared among healthcare providers (including both NHS and voluntary sector providers) through electronic health records. This dataset includes decedent patient records spanning from 2015 to 2023. This EPaCCS is commissioned across the Bradford and Airedale districts, serving a combined population of 585 000 with approximately 4800 deaths per year. Approximately 48% of all deaths in this area had an EPaCCS record in 2018/19.^68^ The anticipated number of records for inclusion is 17 000 decedent records.

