### Analysis

The data from each of the three distinct EPaCCS will be analysed separately. Individual patient-level EPaCCS data will be accessed and cleaned for each of the three systems. The study will categorise the data into social determinants of health (age, gender, ethnicity, social deprivation), clinical characteristics and elements relating to ACP. The social determinants of health have been identified from existing literature for being associated with poor health experiences and outcomes. The study will assess the completeness of variables in the data, examining patterns of missing data at the individual level and identifying any outlier records. Based on the characteristics of missing data, the study will adopt an appropriate approach to treating missing data for statistical analysis. Several methods will be considered that are appropriate for missing at random and not missing at random data. Though, it is assumed that the missing mechanism will be missing not at random. However, no robust methods of imputing missingness in the independent variables with a missing not at random mechanism have been identified. If imputation was carried out, a sensitivity analysis will be conducted to compare parameter estimates with/without imputation. Missing values for key outcomes will be imputed using gender, age, comorbidity, cause of death, IMD and/or study area.^45^ For each ACP element, documented decisions will be categorised to create an outcome (binary or ordinal) variable for inclusion in logistic regression modelling of the relationship between each of these outcomes, as distinct analyses, and social determinants of health, adjusting for major confounding variables and consideration of random effects/fixed effects (eg, comorbidity). Confounders will be selected using expert knowledge, existing literature, and the completeness and availability of the data. Using the London and Leeds datasets, a dichotomised binary outcome of whether or not a patient has an EPaCCS record will be created for logistic regression, modelling the association between the creation of EPaCCS records and social determinants of health. The study will identify both similarities and differences between the creation, use and content of EPaCCS records in the three EPaCCS cohorts. Mindful of the reported challenges associated with the interoperability of EPaCCS data,^46^ the comparison of datasets will be cautiously approached. We will examine the impact of the significant increase in EPaCCS records in London,^47^ and potentially the two other cities, following the outbreak of COVID-19 in March 2020 in terms of the documentation and completeness of ACP elements within the EPaCCS records. We will carry out a secondary analysis (sensitivity analysis) excluding individuals whose records were created during the COVID-19 pandemic after examining the data and the trend in the creation of EPaCCS records.

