
### Work package 1 outputs

WP1 will provide evidence of the variation in the uptake of EPaCCS across the three regions in the UK and will identify factors associated with unequal EPaCCS access. The study will describe similarities and differences in the content and creation of EPaCCS which will inform the development of standardised EPaCCS in the future. We will work with key stakeholders (EPaCCS providers, ICBs and health professionals) and in close collaboration with local populations to ensure those who promote end-of-life care decision-making facilitated by EPaCCS are more accessible and acceptable to individuals across the social strata. This will also include bespoke training for health professionals in culturally competent and literate care to enable end-of-life care discussions and decision-making.

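### Uptake is counted by record creation date, but the Leeds and Bradford sets hold decedents only, so their last one to two years may be under-counted and raw counts cannot compare regions

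*Protocol article*

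**What the plan says.** The section on work package 1 fixes the measure of uptake: "The uptake of EPaCCS will be evaluated by describing the number of records created across different time periods and locations". Table 1 (Data sources) describes the data behind it.

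- Leeds: "This dataset encompasses decedent patient records spanning from 2015 to 2023", and "The anticipated number of records for inclusion is 15 500 decedent records".
- Bradford: "This dataset includes decedent patient records spanning from 2015 to 2023", and "The anticipated number of records for inclusion is 17 000 decedent records".
- London (the Coordinate My Care register): 140 000 records, "of which 100 000 are for deceased patients". The other 40 000 are not recorded as deceased.

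Table 2 assigns these same three sets to the descriptive objectives 1A to 1C. Under Work package 1 outputs the article promises: "WP1 will provide evidence of the variation in the uptake of EPaCCS across the three regions in the UK". The work package 1 Analysis section also uses the creation trend for the COVID-19 sensitivity analysis, which is to be done "after examining the data and the trend in the creation of EPaCCS records".

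**The concern.** In a decedent-only extract, a record appears only if its owner has died by the cut-off. A record made in early 2015 has had almost nine years in which to qualify, and one made in late 2023 only weeks. A table of records by creation year therefore tends to drop at its right-hand end even when clinicians create records at a steady rate, and the missing records are those of people who live longer after planning.

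London keeps records of people not known to have died and the other two sites do not, so the shape of the series differs between locations for a reason unrelated to uptake. A raw count also carries no denominator, although the regions differ about 15-fold in population.

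What is at stake is a descriptive output of work package 1: a decline in recording in Leeds and Bradford after the pandemic, or a ranking of regions, that the data do not support.

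**Working it through.** The article gives no uptake trend and no creation-to-death interval, so there is no stated figure to reproduce. The interval below is an assumption, shown over a range.

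**1. Truncation under constant creation.** Assume a constant creation rate, an exponential time from creation to death with median m years, and inclusion only if death occurs by the end of 2023. Put λ = ln 2 / m and u = (1 − e^(−λ)) / λ. The captured share of records created k calendar years before 2023 is 1 − e^(−λk) × u.

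| Median | λ per year | u | 2023 | 2022 | 2021 | 2020 | Apparent change, 2022 to 2023 |
|---|---|---|---|---|---|---|---|
| 3 months | 2.773 | 0.338 | 66% | 98% | 100% | 100% | 0.662/0.979 − 1 = −32% |
| 6 months | 1.386 | 0.541 | 46% | 86% | 97% | 99% | 0.459/0.865 − 1 = −47% |
| 12 months | 0.693 | 0.721 | 28% | 64% | 82% | 91% | 0.279/0.639 − 1 = −56% |

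True change is zero in every row.

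**2. What would shrink it.**

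- *True growth.* Multiply the 2023/2022 ratio by 1 + g. At 10% a year the apparent change is −26%, −42% and −52% for the three medians. At 20% it is −19%, −36% and −48%. With a median of only 1 month and 20% growth, the series shows a rise of about 6% instead of 20%: damped, but not a fall.
- *Later capture of deaths.* If deaths are captured for one further year, each share moves one column to the right. The spurious fall becomes about 2% (0.979/0.999), 10.5% (0.865/0.966) and 22% (0.639/0.820).

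**3. Scale of what decedent-only extraction leaves out.** In London, 40 000/140 000 = 28.6% of records are not for people recorded as deceased. If the London ratio of 40 000 to 100 000 applied elsewhere (an assumption), the omitted records would number about 15 500 × 0.4 = 6 200 in Leeds and 17 000 × 0.4 = 6 800 in Bradford.

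**4. Raw counts between regions.** By count the order is London 140 000, Bradford 17 000, Leeds 15 500. Per 1000 population:

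- London: 140 000/8 900 000 = 15.7
- Bradford: 17 000/585 000 = 29.1
- Leeds: 15 500/870 000 = 17.8

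London moves from first to last. These rates cover different periods, and London includes people not recorded as deceased, so they are not uptake estimates. They show only that the order depends on the denominator.

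**The case against.** The strongest reply is that this is one sentence about descriptive tabulation in an exploratory work package, with a full statistical analysis plan still to come. No test uses these counts. Objective 1E and the work package 2 primary outcome are defined among decedents and do not depend on them. That is true and limits the weight of the point. But the article states the measure itself, and that measure does not suit two of the three data sets, so this is more than unstated detail.

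The article does say that differing timescales will be taken into account and that comparison of datasets will be cautious. The first concerns unequal calendar coverage and the second is tied to interoperability. Neither deals with records lost because the person is still alive.

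A reader might infer that the plan has no denominator anywhere. It does. Objective 1E models having a record or not among decedents in North West London and in Leeds 2021–2023, and the Ecological analysis section defines deaths with a record over all deaths. What remains uncovered is Bradford, Leeds before 2021, and the uptake measure as worded.

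A reader might also infer that a COVID-19 peak and return to baseline would be largely artefact. The figures do not support that: 82% to 100% of 2020–2021 records are captured. The surge the article describes is in London, which is not decedent-only, and it names the other two cities only as a possibility. Nor does the article say that the trend alone sets the exclusion window.

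**Conclusion.** The point holds in a limited form. If the Leeds and Bradford sets require death by the end of 2023, their creation counts for 2023, and with longer intervals for 2022, are too low. Under constant creation and assumed medians of 3, 6 and 12 months, the visible 2022-to-2023 fall is about 32%, 47% and 56%. The shortfall of 34%, 54% and 72% against true 2023 creation is a different quantity and should not be read as the visible fall, because 2022 is truncated too.

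It would also be too strong to say that a false fall is certain. The size rests on an interval the article does not give, on true growth, and on whether the years 2015 to 2023 refer to death or to creation, which the text leaves open. Capture of deaths after 2023 would reduce the bias.

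For the COVID-19 work, the effect is confined to the post-pandemic level used to judge when the increase ended. Separately, raw counts cannot carry the between-region statement about uptake.

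**What to change.** - **Main measure.** Report uptake as the proportion of deaths with a record, by year of death, wherever all deaths are held (North West London; Leeds 2021–2023). This extends the ratio already defined under Ecological analysis.
- **Bradford, and Leeds before 2021.** Report decedents with a record by year of death over that year's deaths in the area. The single rounded figure of about 4800 deaths a year in Table 1 should not serve as a fixed denominator for Bradford, because it ignores any change in deaths over the period, including during the pandemic.
- **Creation-date counts from decedent-only sets.** Either end the series a fixed interval before the last captured death, or count only records followed by death within that interval and label them so. State whether the years 2015 to 2023 refer to death or creation, and give the last date to which deaths are captured.
- **COVID-19.** Do not read the 2022–2023 counts in Leeds and Bradford as a trend, or use them to set the end of the exclusion window.

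The cost is revised wording, a retabulation of data mostly already held, and year-specific death totals for Bradford and early Leeds. The creation-date series ends earlier, and the fixed-interval version describes only records made within that interval before death, so it omits people who planned earlier.

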### Analysis

The data from each of the three distinct EPaCCS will be analysed separately. Individual patient-level EPaCCS data will be accessed and cleaned for each of the three systems. The study will categorise the data into social determinants of health (age, gender, ethnicity, social deprivation), clinical characteristics and elements relating to ACP. The social determinants of health have been identified from existing literature for being associated with poor health experiences and outcomes. The study will assess the completeness of variables in the data, examining patterns of missing data at the individual level and identifying any outlier records. Based on the characteristics of missing data, the study will adopt an appropriate approach to treating missing data for statistical analysis. Several methods will be considered that are appropriate for missing at random and not missing at random data. Though, it is assumed that the missing mechanism will be missing not at random. However, no robust methods of imputing missingness in the independent variables with a missing not at random mechanism have been identified. If imputation was carried out, a sensitivity analysis will be conducted to compare parameter estimates with/without imputation. Missing values for key outcomes will be imputed using gender, age, comorbidity, cause of death, IMD and/or study area.^45^ For each ACP element, documented decisions will be categorised to create an outcome (binary or ordinal) variable for inclusion in logistic regression modelling of the relationship between each of these outcomes, as distinct analyses, and social determinants of health, adjusting for major confounding variables and consideration of random effects/fixed effects (eg, comorbidity). Confounders will be selected using expert knowledge, existing literature, and the completeness and availability of the data. Using the London and Leeds datasets, a dichotomised binary outcome of whether or not a patient has an EPaCCS record will be created for logistic regression, modelling the association between the creation of EPaCCS records and social determinants of health. The study will identify both similarities and differences between the creation, use and content of EPaCCS records in the three EPaCCS cohorts. Mindful of the reported challenges associated with the interoperability of EPaCCS data,^46^ the comparison of datasets will be cautiously approached. We will examine the impact of the significant increase in EPaCCS records in London,^47^ and potentially the two other cities, following the outbreak of COVID-19 in March 2020 in terms of the documentation and completeness of ACP elements within the EPaCCS records. We will carry out a secondary analysis (sensitivity analysis) excluding individuals whose records were created during the COVID-19 pandemic after examining the data and the trend in the creation of EPaCCS records.

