### Missing data considerations

Individual-level missing data of the primary outcome variable (place of death) will be excluded from the multivariable analysis. However, in handling missing data related to covariates, those with incomplete data will be identified for a thorough characterisation of the missingness. Depending on the type of data and the level and mechanism of missingness, individual patients without matching covariate data may be excluded from the multivariable modelling. In doing so, we would also be mindful that by excluding such patients, modelling could be subject to biases, for example, due to under-reporting. Hence, we may consider imputing missing data, with sensitivity analysis to determine the effectiveness of imputation on the model outputs.

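### The one missing-data check the plan names for work package 1 does not vary its own missing-not-at-random assumption, so agreement between the two estimates would not show robustness

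*Protocol article*

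**What the plan says.** The statements are in the Analysis section of work package 1 in the protocol article, in this order:

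- Methods are left open: "Several methods will be considered that are appropriate for missing at random and not missing at random data".
- The mechanism is then assumed: "it is assumed that the missing mechanism will be missing not at random".
- For covariates, the protocol reports that "no robust methods of imputing missingness in the independent variables with a missing not at random mechanism have been identified".
- The one named check follows, and it is conditional on imputation being done: "a sensitivity analysis will be conducted to compare parameter estimates with/without imputation".
- A predictor list is given, but for outcomes: "Missing values for key outcomes will be imputed using gender, age, comorbidity, cause of death, IMD and/or study area". No imputation model is stated for incomplete covariates.

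No delta-adjusted, pattern-mixture or bounding analysis is named. No missingness rate is given for any variable, and no rule says how agreement or disagreement between the two estimates will be read.

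**The concern.** A sensitivity analysis should move the assumption that is in doubt. Here that assumption is MNAR. The text adopts no MNAR imputation method for covariates, so an imputation of a covariate would by default be a standard one under missing at random. Setting it beside the complete-case estimate compares two analyses, neither of which varies how the unseen values depart from the observed ones.

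Objective 1D estimates associations between social determinants, ethnicity among them, and completion of advance care planning (ACP) elements within a record. A sparsely filled record may lack both ethnicity and the ACP fields, so missing ethnicity may depend on the 1D outcome. If that dependence also differs by ethnic group, the ethnicity OR is biased. The named comparison could then show two matching figures, and a biased equity estimate would look stable. The outputs section of work package 1 says the results will identify factors linked to unequal access and inform training.

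**Working it through.** The plan gives no figure to reproduce. The check is algebra, then illustrations under assumed rates.

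**1. Complete-case OR.** Let X be ethnicity (1 = minority), Y the outcome (1 = ACP element completed), and o(x,y) the probability that ethnicity is recorded. Then

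complete-case OR = true OR × S, where S = [o(1,1) × o(0,0)] / [o(1,0) × o(0,1)].

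If o depends on X alone, on Y alone, or is a product of the two, S = 1 and there is no bias. MNAR by itself therefore does not imply bias; joint dependence that does not factorise does.

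**2. Imputed OR.** Imputing X from Y under missing at random draws from the distribution of X given Y among those with X recorded. The completed data keep that distribution at each level of Y, so the imputed OR also equals true OR × S. The two agree whatever S is. Worked 2×2 cases with true OR 0.667:

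| Missingness depends on | Complete-case OR | Imputed OR |
|---|---|---|
| X only | 0.667 | 0.667 |
| X and Y | 0.948 | 0.948 |
| X and Y, stronger | 1.333 | 1.333 |

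**3. Size under assumed rates.** Assume logit P(ethnicity missing) = −2.2 + 0.8 × (element not completed) + 0.5 × (minority) + k × (both). Ethnicity is then missing in 10.0% (majority, completed), 19.8% (majority, not completed) and 15.5% (minority, completed). The fourth cell (minority, not completed) depends on k.

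S = (0.8455 × 0.8022) / (0.9002 × o), where o is the recorded fraction in the fourth cell:

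| k | Missing in fourth cell | S = complete-case OR if the truth is 1.00 |
|---|---|---|
| 0 | 28.9% | 1.06 |
| 0.3 | 35.4% | 1.17 |
| 0.6 | 42.6% | 1.31 |
| 1.0 | 52.5% | 1.59 |

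A simulation with one further covariate, n = 17 000 (the anticipated Bradford size) and ten imputations that included the outcome gave complete-case and imputed ORs of 1.16 and 1.16, 1.31 and 1.31, and 1.59 and 1.59 for k = 0.3, 0.6 and 1.0. The largest log-OR gap was 0.024. Applied to a real shortfall of OR 0.667, S at k = 1.0 gives 0.667 × 1.586 = 1.06, so its direction would be lost.

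**4. Where the estimates separate.** Simulations with N = 400 000 and about 25–32% missing (assumed):

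| Setting | True | Complete-case | Imputed |
|---|---|---|---|
| X-by-Y missingness, auxiliary in the imputation model | 0.70 | 1.11 | 1.05 |
| Missingness on X, Y and auxiliary; auxiliary in the model | 0.70 | 0.84 | 0.77 |
| Missingness through Y-by-auxiliary; auxiliary in the model | 0.71 | 0.53 | 0.66 |
| OR of another, complete covariate | 0.74 | 0.80 | 0.72 |
| Missingness on X only, outcome left out of imputation | 0.70 | 0.71 | 0.78 |

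In the first row the gap shows ln(1.111/1.050) / ln(1.111/0.703) = 0.056/0.458, about 12% of the bias. In the second to fourth rows the imputed value is nearer the truth; in the last the complete-case value is. A gap does not say which to believe.

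**5. What shift would be needed.** Under the step 3 model, the log-odds of minority ethnicity among those missing exceed those among the recorded by 0.5 where the element was completed and by 0.5 + k where it was not: 0.8, 1.1 and 1.5 for k = 0.3, 0.6 and 1.0. With outcome-specific shifts at these values, delta-adjusted imputation returned ORs of 1.00 (k = 0.3) and 0.99 (k = 0.6). A common shift of 0.5 returned 1.09 and 1.20.

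**The case against.** **The analysis plan may settle this.** The protocol makes imputation conditional, keeps MNAR methods under consideration and promises a full statistical analysis plan. A grid of shifts is detail an article would leave to that plan. This stands for the detail. It does not answer the point, which is that the one check the article states does not address the mechanism the article states.

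**A reader might infer that the two estimates nearly always agree.** They do not. Step 4 shows separation with informative auxiliaries, for complete covariates, or when the outcome is left out of the imputation model. The registers hold candidate auxiliaries such as diagnosis and performance status. Close agreement is specific to the incomplete covariate's own OR, with the outcome in the model and weak auxiliaries.

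**A reader might infer that the plan will treat agreement as proof of robustness, or that it denies any MNAR method exists.** It says neither. It says estimates will be compared, and that no robust imputation method for covariates was identified. Approaches other than imputation stay open.

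**A reader might extend the point to deprivation, objective 1E or work package 2.** Support is weak. On deprivation, the protocol says "an IMD score will be created for each patient based on their postcode", and the index is itself a listed imputation predictor. For 1E, the North West London data are described as detailed on ethnicity, and the sparse-record mechanism concerns ACP fields. In work package 2, Missing data considerations mentions "sensitivity analysis to determine the effectiveness of imputation on the model outputs" without defining the comparison, and there ethnicity is a confounder, not the exposure.

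**The illustrated sizes are assumed.** They are, and the larger ones need 35% to 52.5% missing ethnicity in one cell. Delta adjustment also recovered the truth only when given the generating shifts, which are unknown in practice. It displays sensitivity; it does not correct bias.

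**Conclusion.** The concern holds in a limited form. The named comparison does not vary the MNAR assumption, so agreement between the two estimates is not evidence of robustness to MNAR, and disagreement does not identify the better one. For the ethnicity OR in objective 1D, the two can match exactly while sharing a bias.

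The size cannot be stated from the protocol, which gives no missingness rates. Under the assumed rates, a true OR of 1.00 becomes 1.06 to 1.59 in the complete cases. This rests on three assumptions: that missing ethnicity depends jointly on ethnicity and ACP completion, that the outcome is in the imputation model, and that auxiliaries are weak. If missingness depends on ethnicity alone, the complete-case OR is unbiased. The documents do not show that the planned estimates are biased, only that the stated check could not reveal it.

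**What to change.** In the Analysis section of work package 1, and in the analysis plan:

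- Keep the comparison with and without imputation as description only.
- Name an MNAR sensitivity analysis for ethnicity, and for any other social determinant with material missingness: delta-adjusted (pattern-mixture) multiple imputation with the outcome in the imputation model.
- Pre-set the range of log-odds shifts, let them differ by outcome level, and make the range wide enough for plausible departures. A grid stopping at ±1 would not reach the shifts of 1.1 and 1.5 in step 5.
- Report the ORs over the grid and the shift at which each equity conclusion changes.
- Reword the sentence on robust methods to say that MNAR cannot be corrected from the data but will be explored by this analysis.

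The cost is a few sentences and repeated runs of an imputation model already contemplated. The downside is more tables and a range of ORs rather than one figure.
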